## Methods and analysis

This pragmatic critical-realist implementation study^30^ will use the Integrated Promoting Action on Research Implementation in Health Services (i-PARIHS) framework^31 32^ in six case studies. Each case comprises a specialist palliative care team working with 4–6 care homes each.

i-PARIHS represents an integrated approach, recognising that most implementation is complex, requiring attention to multiple factors simultaneously for an innovation to be successful. The development of theory is central to i-PAHRIS and enables effective implementation of research evidence into everyday practice.^33^ Programme theories explaining micro changes and transactions, such as working hypotheses or local theories of change, are explored to elucidate core concepts. From these, mid-range theories are developed that have greater explanatory potential to predict and plan for change across different settings.^33^ For this study, theories will be generated regarding (1) influential components of the UK context and (2) the mechanisms of how to implement Needs Rounds in care homes in order to deliver desired outcomes.

Facilitation is also critical for successful implementation.^31^ Facilitators are agents of change who lead or champion an innovation. Facilitators for each case will be identified during phase 1 data collection.^34^ Recognising the likelihood of high turn-over of staff in care homes, at least two key staff members (facilitators) will be identified for each care home.

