Care homes (adopting Needs Rounds as their new standard of care). n=28–36	Located near to the specialist palliative care team Provide care to residents who have high clinical nursing/medical needs Willing to sign a memorandum of understanding with the research team, outlining resident demographics and health service use data, facilitate access to staff for interviews, and engagement in Needs Rounds A range of sizes (focusing primarily on larger care homes, following CQC data indicating lower quality in larger facilities),^46^ sole traders and large corporate provider, and with a range of funding models (NHS/social care and self-funded residents).
Residents (discussed at Needs Rounds in phase 2) Estimate of n=1500	Resident in a collaborating care home in one of the six case study locations An anticipated life-expectancy of less than 6 months At risk of dying without appropriate planning in place Experiencing inadequately managed bio-psychosocial symptoms Not engaged in any current safeguarding investigations Able to provide their own informed consent
Relatives (completing outcome measures in phase 2) n=300	The relative of a resident who was discussed in Needs Rounds Able to provide their own informed consent.
PPI evaluation n=15	Coinvestigator or a member of one of the case study sites Able to provide their own informed consent

CQC: Care Quality Commission; NHS: National Health Service

For the quantitative sample, the average size of the care homes is anticipated to be 52 beds, and the rate of emergency admission to hospital to be 0.173 per bed within the 4-month period,^37^ with an average of 9 admissions per care home. A sample of 30 care homes would allow change to be identified in the hospitalisation rate of 0.02 per bed (α=0.05, β=0.2, ΔSD=0.040). This is sufficient to detect a clinically meaningful change in the primary outcome (reduction of one hospitalisation per 4 month period in a typical care home) for the quantifiable data in phase 2.

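### The assumed SD of change (0.040 per bed) is about half the chance variation implied by the plan's own 9 admissions per home, so power for the target change is about 25%, not 80%

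*Protocol article*

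**What the plan says.** The sample-size paragraph after Table 1 (Target sites and population) sets out these inputs:

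- Home size: "the average size of the care homes is anticipated to be 52 beds".
- Baseline rate: "the rate of emergency admission to hospital to be 0.173 per bed within the 4-month period", which it converts to a count, "with an average of 9 admissions per care home".
- The calculation: "A sample of 30 care homes would allow change to be identified in the hospitalisation rate of 0.02 per bed (α=0.05, β=0.2, ΔSD=0.040".
- The conclusion: "This is sufficient to detect a clinically meaningful change in the primary outcome", defined as a "reduction of one hospitalisation per 4 month period in a typical care home".

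The section on estimating the treatment effect compares one 4-month window before implementation with months 9–12 of delivery, using a paired t-test on the hospitalisation rate. The article gives no derivation of the 0.040.

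On the number of homes, Methods and analysis says of the six cases: "Each case comprises a specialist palliative care team working with 4–6 care homes each". That allows 24 to 36 homes. Table 1 has: "Care homes (adopting Needs Rounds as their new standard of care). n=28–36".

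**The concern.** An SD of 0.040 per bed in a 52-bed home is 2.1 admissions. A home expecting 9 admissions will vary by about 3 from one window to another by chance alone, and a difference between two windows varies more than either window. The assumed SD therefore looks too small for the event counts given beside it.

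The power statement tells readers how to interpret the result. If power is really about a quarter, a non-significant result says little about whether one admission per home was avoided, yet the plan invites readers to take it as informative. A significant result would have to come from an estimate well above the target. The same estimate and its 95% confidence interval drive the cost-benefit analysis and the 5-year savings projections, where the interval will be about twice as wide as the stated SD suggests.

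**Working it through.** **Inputs (all from the protocol article):** 52 beds; 0.173 admissions per bed per window; target change 0.02 per bed; SD of change 0.040; 30 homes; α = 0.05, taken as two-sided because sidedness is not stated; 80% power; paired t-test on home-level rates.

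**1. The plan's own figure.** Paired normal formula, n = ((z₀.₉₇₅ + z₀.₈₀) × SD / δ)²:

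- n = ((1.960 + 0.842) × 0.040 / 0.02)² = 31.4, so 32 homes.
- Power at 30 homes: Φ(0.5 × √30 − 1.960) = Φ(0.779) = 78%.
- Detectable change at 30 homes: 2.802 × 0.040 / √30 = 0.0205, which rounds to 0.02.

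The figure of 30 therefore reproduces to within rounding. By noncentral t, power is 75% and 34 homes are needed. The formula is not the problem.

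**2. SD implied by the plan's counts.** 52 × 0.173 = 9.0 admissions before. One fewer gives 8 after. For independent Poisson counts the variance of the difference is the sum of the two means.

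| Assumption | Variance (admissions²) | SD per bed |
|---|---|---|
| Stated ΔSD | (0.040 × 52)² = 4.3 | 0.040 |
| Poisson, 9 then 9 | 18 | √18/52 = 0.0816 |
| Poisson, 9 then 8 | 17 | √17/52 = 0.0793 |
| At most one admission per bed, 0.173 in both windows | 2 × 52 × 0.173 × 0.827 = 14.9 | 0.0742 |
| At most one admission per bed, 0.173 then 0.153 | 52 × (0.173 × 0.827 + 0.153 × 0.847) = 14.2 | 0.0724 |
| Poisson with 1.5-fold overdispersion, 9 then 8 | 25.5 | 0.0971 |

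The stated variance is about a quarter of the Poisson variance (4.3/17 to 4.3/18). A single window already has SD √9/52 = 0.058, so reading 0.040 as a one-window SD does not help. Chance alone would give 0.040 only in homes of (0.173 + 0.153)/0.040² ≈ 204 beds.

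**3. Power for 0.02 per bed (two-sided paired t) and what 80% would need.**

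| SD of change | 24 homes | 28 homes | 30 homes | 36 homes | Homes for 80% |
|---|---|---|---|---|---|
| 0.040 (stated) | 65% | 72% | 75% | 83% | 34 |
| 0.0816 | 21% | 24% | 25% | 30% | 133 |
| 0.0793 | 22% | 25% | 27% | 31% | 126 |
| 0.0742 | 24% | 28% | 30% | 35% | 110 |
| 0.0724 | 25% | 29% | 31% | 36% | 105 |
| 0.0971 | 16% | 18% | 19% | 22% | 187 |

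Simulated paired t-tests with 30 equal 52-bed homes gave 26% power, whether or not homes differed in their underlying rate. With unequal bed numbers (coefficient of variation 0.4, an assumed value) power was 23%.

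**4. Detectable change with 30 homes at 80% power.** At the Poisson SDs this is 0.042 to 0.043 per bed. Multiplied by 52 it is about 2.2 admissions; divided by 0.173 it is a 24–25% reduction. The plan's target is 0.02/0.173 = 11.6%.

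**5. What a significant result would require.** The critical t on 29 degrees of freedom is 2.045. The smallest significant estimate is 2.045 × 0.0793/√30 = 0.0296 to 2.045 × 0.0816/√30 = 0.0305 per bed, about 1.5 times the 0.02 target.

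**The case against.** No passage derives or defends 0.040, so the case on the other side is about weight and certainty.

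- *Hospitalisation is not the study's main outcome.* The Abstract and Outcomes sections make the qualitative question primary and health service use secondary. The sample-size paragraph calls hospitalisation primary only for the quantifiable phase 2 data. This stands and limits the reach of the point, but this is the main quantitative comparison and the basis of the economic analysis.
- *Poisson variation is an assumption.* True. But allowing at most one admission per bed lowers the SD only to 0.072–0.074, and variation in risk among residents, which could lower it a little further, does not plausibly bring it to 0.040. Repeat admissions, home-specific time trends, varying effects and unequal home sizes push it up.
- *Pairing reduces the SD.* Pairing removes stable differences between homes, and the 0.08 already assumes that none remain. Reaching 0.040 would need a correlation of about 0.76 between the two windows' chance fluctuations (1 − 4.3/18), beyond any home effect.
- *The economic model already uses both confidence limits.* This largely stands. The model is not conditional on significance, so exaggeration matters mainly if a significant point estimate is singled out.
- *The 75% against 80% gap is only t against normal.* Agreed; it is a side point, as is the mismatch in home numbers, since 30 lies within both ranges.

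**Conclusion.** The concern holds. The SD of 0.040 cannot be squared with 9 admissions per 52-bed home; the plan's own counts imply about 0.08 under Poisson variation. With 30 homes, power for the stated change is 25–27%, rising to 30–31% with at most one admission per bed and falling to about 19% with 1.5-fold overdispersion. The statement that the sample suffices to detect one fewer admission per home is therefore wrong as written. The conclusion rests on a two-sided test and on admissions varying roughly as Poisson or binomial counts, independently between windows. The qualitative primary outcome is not affected.

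**What to change.** Keep 30 homes and rewrite the sample-size paragraph:

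1. Replace the SD of change with about 0.08 per bed, and say that it follows from about 9 admissions per home per window under Poisson variation.
2. State that 30 homes give about 25% power for a change of 0.02 per bed, and that the change detectable with 80% power is about 0.043 per bed, or 2.2 admissions per home.
3. Remove the claim of sufficiency for one admission. Present the hospitalisation result as an estimate with a 95% confidence interval, and say that a non-significant result does not exclude the target effect.
4. Make the two ranges of home numbers (24–36 and 28–36) agree, and quote power across the agreed range.

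If the investigators have data supporting 0.040, they should give the source and explain how it fits with 9 admissions per home.

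The cost is one reworded paragraph and a less favourable stated power. It needs no extra homes or data collection.

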### Project phases

#### Phase 1: codesigning Needs Rounds for the UK context

The purpose of phase 1 is to conduct theoretical modelling to generate programme theories about how Needs Rounds could be used. Programme theories will be developed by examining what elements of Needs Rounds would work, for whom, in what circumstances and why, in the UK context. Data will be collected through 40 semistructured individual or small-group interviews with key stakeholders from the six case study sites. Interviewees will be asked to describe their local context, such as services’ geography, policy, structure, funding and practice elements.

Contextual factors can significantly impact implementation; therefore, understanding and being responsive to these components are essential.^34^ Key contextual factors will be mapped out in the phase 1 interviews, drawing on the i-PAHRIS inner (micro and meso) and outer level (macro) contextual factors.^38^ The former includes individual and organisational components such as culture, leadership, experience of innovation, and absorptive capacity, while the latter examines the wider health system, including policy drivers, regulatory frameworks, and interorganisational networks and relationships. Services’ geography, policy, structure, funding and practice elements will then be refined in workshops to codesign Needs Rounds. Differences between the UK and Australia will be described.

Relevant documentation (eg, service policies) will be collated to help develop realist theories regarding how implementation would work in practice and what might influence implementation in each case study site, to identify contextual factors, mechanisms and outcomes (CMO) (figure 1).

**Figure 1 F1:**
[figure not shown]
Contexts, mechanisms and outcomes derived from the Australian trial of Needs Rounds.

#### Phase 2: implementing and evaluating Needs Rounds

Phase 2 will test and refine the programme theories generated in phase 1, by implementing, adapting and evaluating UK Needs Rounds in the six case study sites. Interviews will be conducted after 4 months (capturing early adoption), 8 months (mid-range) and 12 months (longer term) of implementation. Interviews will collect prospective data on process and mechanisms of change and examine the CMOs/theories, acceptability, appropriateness, feasibility, implementation cost, coverage, sustainability and adherence.

Phase 2 will also incorporate a qualitative evaluation of the impact, outcomes and process of PPI throughout the study. A survey will be conducted with care homes not engaged in the implementation after the phase 2 workshop to garner feedback on the fit of the UK Needs Rounds approach for their service.

Key study phases are depicted in figure 2.

**Figure 2 F2:**
[figure not shown]
Study phases.

### Outcomes

The primary outcome is to determine *what works, for whom, in what circumstances,* for UK Needs Rounds. Secondary outcomes focus on health service use, alongside quality of death and dying, staff capability to adopt a palliative approach, and family perceptions of care. The core economic outcome is the total change in health and social care service costs that result from the intervention.

### Data collection

Data will be collected for each case from interviews and site documentation. Activity logs will also be generated, to capture time spent by all parties, and additional work generated beyond the Needs Rounds meeting. Environmental/contextual data will draw from conceptual work by Estabrook *et al*^39^ and i-PARIHS^34 38^ and be qualitative in nature to dynamically explore each care home’s culture. Interview topics will cover, for example, provider and funding types, leadership, culture, including attitudes towards residents and whether staff feel supported and valued, time/space, staff/resident turnover, introduction of new policies/procedures, and prioritisation of the intervention in workload.

Needs Rounds discussions will be audio-recorded. This will allow analysis of adaptations made by clinical teams for their local areas, alongside the breadth/depth/content of case-based education provided.

Staff capability of adopting a palliative approach (CAPA) will be assessed on a nine-item validated self-report questionnaire.^40^ CAPA has a unidimensional scale; higher scores indicate greater capacity. Internal consistency reliability is very high with a Cronbach’s alpha of 0.95, and split-half-reliability coefficient of 0.93.^40^ Self-complete measures will be taken at baseline from all nursing assistants/care assistants and RNs, and prospectively each month with staff attending Needs Rounds. Final assessment will be taken from all NAs and RNs following the 12-month trial period.

The Quality of Death and Dying Index^41^ (QODDI) will be completed by care home staff for each decedent resident prospectively during implementation. This 17-item questionnaire examines four domains: symptom control, preparation, connectedness and transcendence, on a 0–10 scale, where higher scores indicate a better experience. The Cronbach’s alpha for the QODDI total score is 0.89. Following correspondence with the scale’s originator confirming psychometric robustness of excluding items, one item on access to euthanasia will be removed, as this is not legal in the UK. The QODDI was designed for completion by relatives; however, staff are more likely to have seen the resident in the weeks prior to death so staff completion will result in more reliable and valid data.

Family perceptions of care will be captured from relatives of residents who are discussed at Needs Rounds, using the CANHELP lite.^42^ Twenty-two items from the second half of the questionniare will be used to collect family self-reported data of satisfaction with care. The Cronbach’s alpha for the total score is 0.88–0.94. A family will only be asked once to complete this measure, even if the resident is discussed at Needs Rounds more than once.

Resident data collection will focus on demographic information and health service use (table 2). Data will be collected from the care homes by care home staff. Training will be provided to ensure robust data collection and reporting. This will be summary level data to ensure anonymity.

**Table 2 T2:** Resident data collection

Type	Variables
Demographic information	Age Ethnicity First language Charlson Comorbidity Index
Deaths	Number of deaths Preferred place of death Actual place of death
Health service use	Clinical role seen in primary care Hospital admissions: Name of hospital Duration of admission Specialty/ward Mode of transport to hospital
Assessments and interventions triggered by Needs Rounds	Physical assessments Clinical investigations, for example, blood/urine tests Referrals to other NHS services Changes in medicines Syringe drivers

Economic evaluation will be based on the intervention and health service cost elements identified in tables 3 and 4. The costs of hospitalisation will be constructed from resident-level data on length of stay collected by the care homes, and costed using the National Tariffs and hospital specific Patient Level Information and Costing System data for both England and Scotland. Total costs for the each of the pre and post periods will be calculated by summing these costs across all residents admitted to hospital from a given site; the benefit is the difference between prehealth and posthealth service-use costs.

**Table 3 T3:** Intervention cost elements

Cost type	Cost detail	Measurement of costs
Direct costs	Intervention costs on-site: Staff time Travel Consumables and equipment Workshop costs	Included within the project budget and therefore directly recorded. Where appropriate additional detail will be collected directly from the care homes.
	Additional NHS staff time attending care home Additional prescriptions	Estimated in the SoECAT, with additional costs recorded by intervention staff as required.
	Costs of taxis to transfer residents to hospital	Collected from care home sites in a proforma through interviews.
Indirect costs	Wider additional costs incurred by the care home, including: Changes in their staffing Changes to facilities (ie, use of rooms), or overheads as a result of hosting the intervention.	These changes, and their associated costs, will be collected from care homes in a proforma through the interviews
Intangible costs	Inconvenience to staff, residents, family and carers as a result of the intervention.	These will not be measured directly, but will be explored in the qualitative interviews.

**Table 4 T4:** Health service cost elements

Cost type	Cost detail	Measurement of costs
Direct costs	Costs of ambulance journeys	Estimated from the 2019/20 National Tariff Payment System.^47^
	Hospital stay cost	Hospital-specific Patient Level Information and Costing System data for England^48^ and Scotland^49^ on stay costs by age and gender to estimate a day rate to use in the hospital costing.
	Primary care usage	Collected from care home sites in a proforma through interviews
Indirect costs	Wider additional costs incurred by the care home, in connection with resident hospital admissions, including staffing, travel, equipment or facilities.	These costs will be collected from care homes in a proforma through the interviews
Intangible costs	Inconvenience to residents and their family/carers arising from hospitalisation	These will not be measured directly, but will be explored in the qualitative interviews in the main study.

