### Estimating the cost effectiveness of the intervention on health service outcomes

A cost–benefit analysis (CBA) of the intervention will be undertaken. The cost calculation will include both direct and indirect costs to both NHS and care homes delivering the intervention. Benefits are calculated as the change in NHS costs incurred following the intervention. This will be estimated by valuing the reduction in hospital stays and hospital days as a result of the intervention. These will be measured using hospital day rates and ambulance costs. Where possible, data will also be collected on additional costs, such as hospital transfers via taxi and primary care use.

The CBA will be conducted from the perspective of the NHS and Personal Social Services. The costs of the intervention will be compared with the changes in health service costs from reduced hospitalisation. The costs and benefits will be calculated taking account of (1) uncertainty in the estimate of the treatment effect; (2) projected costs over a 5-year period; and (3) spatial variation in cost across jurisdictions. Wherever possible the analytical specification will follow that of the National Institute of Health and Care Excellence (NICE) Reference Case.^44^ While there are also likely to be individual and broader societal benefits arising from the intervention, these are challenging to value in financial terms and beyond the scope of this economic evaluation. They will be explored through the qualitative data collection.

The net benefits of the intervention will be modelled over a 5-year period separately for care homes in (1) England and (2) Scotland, given the estimate of cost savings per care home bed and the total number of care home beds in each jurisdiction, and applying an annual discount rate. These predictions will be modelled at the point estimate for the treatment effect, and also for the upper and lower bounds of the 95% CI around the treatment effect, to provide a range of plausible costs savings over 5 years incorporating the uncertainty in the main study.

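### Tables 3 and 4, on which the economic evaluation is based, have no line for clinical investigations or off-site NHS referrals that Table 2 records as triggered by Needs Rounds

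*Protocol article*

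**What the plan says.** In the protocol article, under Data collection, the scope of the costing is fixed by reference to two tables: "Economic evaluation will be based on the intervention and health service cost elements identified in tables 3 and 4". Both tables are printed.

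Table 2, in the same section, has a category for assessments and interventions that Needs Rounds set in motion. It lists "Physical assessments Clinical investigations, for example, blood/urine tests Referrals to other NHS services Changes in medicines Syringe drivers".

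The direct costs in Table 3 are "Intervention costs on-site: Staff time Travel Consumables and equipment Workshop costs", then "Additional NHS staff time attending care home Additional prescriptions", then taxi transfers to hospital. The measurement note for the second of these rows reads "Estimated in the SoECAT, with additional costs recorded by intervention staff as required". The direct costs in Table 4 are ambulance journeys, hospital stays and primary care usage, the last "Collected from care home sites in a proforma through interviews".

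Under Outcomes, the core economic outcome is the total change in health and social care costs that the intervention brings about. Under Estimating the cost effectiveness of the intervention on health service outcomes, the perspective is the NHS and Personal Social Services, and the cost side is to include direct and indirect costs to the NHS and care homes. Of the benefit, that section says: "This will be estimated by valuing the reduction in hospital stays and hospital days as a result of the intervention".

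**The concern.** The plan attributes certain NHS activity to the intervention and arranges to record it, but the tables that set the scope of the costing give part of that activity no place. A blood or urine test prompted by a round, or a referral to a service outside the home and primary care, is an NHS cost under the stated perspective.

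The benefit side does not pick these items up either. Pre and post service costs are summed over residents admitted to hospital, and the saving is valued from hospital stays and days. The evaluation would then credit avoided hospital use without charging all of the NHS activity generated in avoiding it.

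Referrals are not incidental: Intervention description names referral to relevant specialists among the actions that a round starts. The net benefit per bed is to be scaled to all care home beds in England and in Scotland over 5 years, so an error in cost per home carries into those projections. The planned range from the 95% CI would not reveal it, because that range reflects only uncertainty in the treatment effect.

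**Working it through.** **1. Each Table 2 item set against Tables 3 and 4**

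| Table 2 item (triggered by Needs Rounds) | Line in Table 3 or 4 | Covered? |
|---|---|---|
| Physical assessments | Staff time; NHS staff time at the home | Largely |
| Clinical investigations | None | No explicit line |
| Referrals to other NHS services | NHS staff time at the home or primary care usage, if the referral leads there | In part; off-site services have no line |
| Changes in medicines | Additional prescriptions | Yes |
| Syringe drivers | Not named; device could sit under equipment, drugs under prescriptions, set-up under NHS staff time | Unassigned, not clearly omitted |

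Two gaps remain: investigations, and referrals that lead outside the home and primary care.

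**2. Whether wording elsewhere closes the gaps**

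- The note "Estimated in the SoECAT, with additional costs recorded by intervention staff as required" stands against the row for NHS staff time and prescriptions. It does not extend to tests or off-site services, and its last words leave collection to discretion.
- The activity logs under Data collection capture time and further work. They do not capture the cost of a laboratory test or an outpatient service.
- The cost-effectiveness section allows other costs to be collected where possible, with taxis and primary care as examples. That permits inclusion but does not commit to it.

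**3. Scale, from the document's own inputs**

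The plan states no net benefit, so there is no such figure to reproduce. Its admission figures (Target sites and population) do reproduce:

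- Baseline: 52 beds × 0.173 per bed = 8.996, the stated 9 admissions per home per 4 months.
- Target change: 52 × 0.02 = 1.04, the stated reduction of about one admission per home per 4 months.

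Intervention description gives 8–10 residents per home at each monthly round:

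- Discussions per home per 4 months: 8 × 4 = 32 to 10 × 4 = 40.
- Discussions per admission averted: 32 / 1.04 = 30.8 to 40 / 1.04 = 38.5.

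Let c be the average additional uncosted activity per discussion. The document does not give c; it is an assumption. Cost is then understated by 32c to 40c per home per 4 months. Let A be the cost of one admission, also not given. The understatement equals the whole gross saving at the target effect when:

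- 32 discussions: c = 1.04A / 32 = 3.25% of A.
- 40 discussions: c = 1.04A / 40 = 2.6% of A.

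This is a break-even point, not an estimate. The 1.04 is the change that the sample size was set to detect; the protocol forecasts no saving. A resident may be discussed more than once, and a repeat discussion need not trigger a new test, so c may be well below the cost of a single test or referral.

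**The case against.** The strongest reply is that the tables name broad cost elements and that a journal article leaves the itemised unit-cost list to a fuller document. The declared outcome is total cost change, the cost side promises direct and indirect NHS costs, primary care usage may include some tests ordered through primary care, and the additional-cost wording is open. On this view a missing line is weak evidence of a decision to exclude. It stands in part: the costs could be included without contradicting the stated outcome. But the article does not leave scope open. It ties the evaluation to two printed tables that go down to taxi fares, and following them as written leaves the two items out.

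Three stronger readings are tempting, and the document does not support them.

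- A reader might infer that syringe drivers are left out as well. The equipment, prescription and NHS staff time lines can hold them; the plan only fails to say which does.
- A reader might infer that the gap must always favour the intervention. It does so only where the activity is additional. Some tests and referrals may replace ones that would have happened anyway, and no pre-period count of these items is described.
- A reader might put a sum in pounds on the overstatement, or express it as a share of the saving. Either needs a rate of triggered activity, unit costs and an admission cost, none of which the document gives.

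It is also fair to say that the study's primary outcome is qualitative, so the point touches the economic analysis only.

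**Conclusion.** The point holds for clinical investigations and for referrals to NHS services outside the care home and primary care. The protocol labels both as triggered by Needs Rounds, and the tables that define the economic evaluation give neither a line. That is inconsistent with the stated economic outcome and perspective.

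If the tables are followed as written, and to the extent that the activity is additional and not captured under another line, intervention cost is understated and net benefit is overstated, including over 5 years. The size is unknown. The break-even calculation shows only that a small average cost per discussion would be enough to matter at the design's target effect. The change is worth making before costing begins. It does not affect the sample size or the estimated effect on hospitalisation.

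**What to change.** Add one direct NHS cost line to Table 3: clinical investigations and off-site NHS referrals triggered by Needs Rounds, costed as Table 2 counts × national unit costs. Exclude anything already costed as NHS staff time, prescriptions, equipment or primary care usage, so that nothing is counted twice. State which existing line holds syringe drivers.

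Report net benefit with and without the added line as a sensitivity analysis. With the line, all the recorded activity is treated as additional; without it, none is. Both are needed because there is no pre-period count from which to separate additional from replaced activity.

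The cost is a little extra work to attach unit costs to items already planned for collection, provided that the records show the type of test and the service referred to. The net benefit may also come out less favourable.
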